### Data collection tools, procedures and ethical considerations

#### Data collection tools

##### Women’s surveys

Survey data will be used to ascertain service acceptability, safety, effectiveness and sustainability. The questionnaires were originally derived from those used in IBUS [54] with the addition of some newer validated tools, however there are few tools that have been validated with Australian First Nations peoples. Additional data items will also be collected based on local factors of importance. Table 2 and Additional File 2 lists the validated tools that are used at each survey time point, the outcome the tool measures, and an approximate time for participant completion. Questionnaires will be pretested and piloted with key stakeholders at the rural site, with subsequent revisions (please see Additional File 2: Scales and Tools used in women’s surveys).

##### Staff surveys

To aid in understanding the new service from a workforce perspective, online anonymous surveys will be conducted with eligible service staff including midwives. Surveys will include questions on relevant topics such as team cohesion, organisational collaboration, cultural capability of staff/team members, and suggestions for improvements. The Copenhagen Burnout Inventory [55] and Perceptions of Empowerment in Midwifery Scale-revised (PEMS-revised) [56] will be used, and these have been tested with Australian midwives providing continuity of care and compared with those working in fragmented models [57]. Additional questions about how the MGP operates (caseload, on-call arrangement etc) will be triggered for participants who work in this service model, and can be explored further in Interviews and/or focus groups. Internal piloting of the survey has been completed.

#### Data collection procedures

##### *Women’s surveys*

Survey data collected at three time points will be used to assess outcomes (including women’s experiences) against study aims. There will be the option of completing surveys independently online or with a researcher. Surveys will include questions related to many aspects of maternity care, as well as general life circumstances (e.g. social, emotional, demographic), and other factors such as cultural identity and connection (see Table 2). Surveys are based on previous research work and include relevant validated instruments that have been used by our team previously (see Additional File 2 for scales and tools to be used).

Piloting and early data collection from the IBUS study identified that most women complete the surveys online, while some were receptive to face-to-face completion with researchers entering data directly into a device or being nearby to answer queries during completion. All jurisdictional restrictions for the COVID-19 pandemic will be followed, and additional precautions will reduce risks to participants and researchers (e.g. mask wearing). Where allowable, options will be offered regarding a meeting place of the participants’ choosing. A $20 grocery/department store gift card will be provided after each survey completion, and a small baby gift will be given following the 2-month survey.

When women complete a survey with a researcher, full verbal explanations will be provided. If a survey response(s) indicates a service issue, with the participant’s permission this may be escalated for further action. Researchers will be aware of local hospitals’ complaints processes, and may help or arrange assistance with this. Where online surveys are completed, and a high score and/or selection of ‘trigger’ responses on particular scales are recorded e.g. the Edinburgh Depression Scale (EDS), designated researchers will receive an immediate alert email. Participants will be offered referral (as per IBUS procedures), and triggers and follow ups will be documented.

##### *Women’s yarns & interviews*

Women will have the opportunity to share their birth, pregnancy and parenting stories in an in-depth narrative or semi-structured interview. Interviews will occur in a convenient and practical location and while face-to-face is preferred, they can be conducted on the telephone or by using digital applications such as Skype© or Zoom©. Researchers will use ‘yarning’, a culturally appropriate conversation that is relaxed, flexible and includes developing relationships with participants prior to and during the story-telling [50, 58]. Women who have expressed interest in participation will be contacted by the research team, and eligible women will be offered participation in either a one-to-one, conjoint interview, or a yarning circle (a culturally appropriate group discussion). All women who participate in surveys will be invited to interview.

Yarns will be women-led with freedom for participants to tell their stories as they wish, and to focus on areas of importance to them. We will use a visual 1-page interview guide, developed from themes identified during prior research in the two study sites [14, 59], and ongoing local consultation. Researchers will aim to explore Indigenous perspectives of culturally safe care (acceptability). We will seek to elicit experiences of various relationships throughout engagement in maternity care, and the impacts of these, including on health behaviours and outcomes (e.g. decision making, breastfeeding, smoking cessation). Researchers will digitally audio record interviews for verbatim transcription, and write field notes including observations and reflections. We estimate the interviews will take up to 1 hour and participants’ time will be compensated with a $40 gift card.

During face-to-face interviews (and yarning circles) usually two researchers will be present. Reasons include ensuring coverage and inclusion of all important elements, and for pragmatic reasons e.g. child minding. Usual consent processes will be followed. Women can have a support person present at an interview (particularly relevant for those with complex challenges/needs). If a participant becomes distressed, the interview will cease, and a referral process will be followed*.* The yarning circle data collection process will utilise the interview guide, however, discussion between participants will be facilitated which may generate more extensive exploration of women’s attitudes, views and experiences [60–62].

We anticipate women will be introduced to the BOOSt study via a verbal explanation (word-of-mouth), website, social media, poster information and/or the study flyer. An invitation to participate with a PICF for interview will be provided for women to consider.

##### *Staff/stakeholder interviews & yarning circles*

All relevant personnel who provide maternity care for women having First Nations babies at both research sites will be invited to participate in interviews or discussion groups, which will use an appropriate interview guide. Other stakeholders of relevance may also be invited, including upon employment exit. Attitudes and perceptions regarding Birthing on Country before, during and after implementation will be elicited. ‘Key ingredients’ of a best practice model of maternity care will be identified, as well as evaluation of acceptability, feasibility, and cost-effectiveness (e.g. scope of practice) of the different care models. Other service aspects will also be explored. Qualitative semi-structured or narrative interviews/discussion groups may last about 1 hour. Focus groups will use the same semi-structured interview guide to encourage discussion, in order to lead to a richer understanding of staff/stakeholder perspectives [60–62].

##### *Routinely collected clinical and costing data*

Routinely collected data for each mother/infant dyad in relevant services will be obtained from several sources, predominantly ordinary records. Relevant permissions will be sought from data custodians. Expenditure data will provide detailed patient-level information on hospital inpatient and primary care service costs. Our partners’ routinely collected services data (e.g. check-up and expenditure data) will be analysed.

##### Young women

This study is not specifically targeting young women, however we will follow guidance included in the National Statement (p. 65) asserting that young women “who are mature enough to understand and consent and are not vulnerable through immaturity in ways that warrant additional consent from a parent or guardian” will be invited to consent in their own right [63]. We will also be guided by the standard practice employed for clinical procedures whereby the best interests of each woman will be assessed on an individual basis. The contributions of young women in the IBUS study were substantial so we have successfully applied the relevant processes.

##### Withdrawal from the study

All PICFs state the participant’s right to withdraw, and reiterate that this would not affect participants’ relationships with staff, their employer, supervisors, colleagues, partner organisations or the researchers, and current or future employment.

#### Participant recruitment, informed consent and waiver

 Documented, informed consent for participation, will be obtained from all participants except where a waiver for the use of routinely clinical data has been approved. The main considerations are participant privacy, wellbeing and safety – including cultural safety. This will be assured by ensuring the relevant Participant Information and Consent Form (PICF) has been understood; adherence to the eligibility criteria; and reminding participants of their rights to decline or withdraw participation without consequence.

##### Women’s surveys

Participation in BOOSt research will be encouraged utilising multiple approaches, including face-to-face, and online dissemination, where we aim for maximum awareness at both study sites. Front line health staff will be engaged in dissemination of information (e.g. flyers), inviting potential eligible participants to submit an ‘Expression of Interest’ (EOI) for researcher contact.

Eligible women will be recruited in the third trimester (approximately 28–36 weeks gestation) to complete surveys. This will involve three surveys: during pregnancy, approximately 2 months and 6 months after birth. Women who have already given birth to a First Nations baby in the past 6 months, are also able to participate, by completing the relevant survey. These women will have the option to retrospectively complete earlier questionnaires pending discussion with a researcher. The limitations, risks and benefits of this approach are recognised.

Following relevant ethics guidelines [64], women will be advised they may defer a participation decision until they have had an opportunity to discuss with a trusted person(s). Any questions will be answered. For participants recruited to complete questionnaires, consent will be acquired for the use of routinely collected electronic health records data, and for merging of records with participants’ survey data. Other service user groups whose de-identified data will be analysed in the study will not be asked for consent, as this research meets conditions stipulated in the National Statement for waiver of consent^4^ [63].

##### ‘My story’: women’s yarns

Women having given birth in the catchment areas will be invited to participate in the qualitative component of BOOSt (‘My Story’). Any person meeting the survey inclusion criteria will be eligible.

##### Service providers, staff & other stakeholder interviews and focus groups

Staff and stakeholders involved in planning, managing, supporting and/or providing maternity care to eligible women in our catchment areas will be eligible to participate in individual or group interviews. Recruitment, consent and interviews will follow processes already outlined, using the Staff/Stakeholder Participant Information and Consent Form. Staff who may be exiting or have exited relevant roles will also be invited. Interview participants may be reimbursed for any costs incurred, although it is expected the interview will occur during usual working hours as part of work activities. These participants will be given a small gift (such as coffee vouchers) to thank them for their time.

##### Staff surveys

All staff closely involved in the new Birthing on Country services will be invited to complete surveys about their experiences in the maternity care models and midwives will be asked to complete additional survey sections due to the significant change involved from the usual ways of working. Invitations will be emailed with an electronic anonymous survey link. Completion and submission of the questionnaire will indicate consent for the use of anonymised data.

##### Waiver

For routinely collected data, we have a waiver of consent approved for all cohorts of women. This covers both clinical and costing outcome measures. Initially the data will be collected in a re-identifiable form so we can merge the data from different sources with each participant given a unique identifier. Once this is completed all identifiable data will be removed prior to analysis.

#### Potential for risk, burdens and benefits to participants

 It is believed that the benefits of participation for First Nations women and families, health workers and others, outweighs the risks. Nevertheless, fatigue, anxiety, fears about confidentiality, potential for feeling coerced and potential emotional or psychological distress are all considered, and risk mitigation and response plans implemented.

### Data management, storage, monitoring and analysis

Our First Nations partners have expressed the importance of data sovereignty, the principles and actions of which will be embedded in project governance. Relevant collaborators will ensure sound data processes such as those related to the validating and synthesis of relevant findings, publication and dissemination including feeding back to participants and other Community members, and all decisions related to data sharing. A data management plan will standardise and guide the management of data throughout the study and all datasets will be stored in a secure institutional Microsoft® Sharepoint storage folder, with restricted access. As this system is backed up regularly, it will be the sole database. Approaches we will take to analysing the quantitative and qualitative data are outlined below. The key benefit of using mixed methods we anticipate, will be better informed decision making and action. Participants’ experiences as service users, providers, or as study partners and stakeholders complement observed quantitative data analysis. Analysis will be conducted by, and/or in collaboration with, First Nations team members.

#### Quantitative data

##### Health services and other routinely collected data

Anonymous data from all women attending the site hospitals and health services during the study period will be extracted and analysed by birth model of care. Quantitative analyses will compare maternal and infant health outcomes between the baseline cohort (both sites) and Birthing on Country service innovation cohort (both sites), as well as standard care/concurrent and historical control groups, and non-First Nations groups (where available).

The clinical and costing outcomes data will be derived from routinely collected electronic healthcare databases at each site. Data will be imported to Stata® or Statistical Package for Social Sciences (SPSS®). While data will initially be re-identifiable (with unique study number) all patient identifiers will be removed. Data cleaning and coding decisions will be documented.

Analysis will be performed with the latest version of the appropriate software and statistical significance will be determined at the 0.05 level. Binary outcome measures will be presented using odds ratios with 95% confidence intervals. Several methods will be used to address selection bias e.g. multivariate logistic regression models, linear regression models, propensity score matching (identifies and controls for confounders e.g. the presence of pregnancy complications), and multilevel modelling controlling for clustering factors. Longitudinal outcomes will be analysed with generalized estimating equations to account for the correlation between observations repeated in the same person. We will use trend analysis to compare rates of preterm birth between First Nations and non-First Nations women, which will demonstrate if this inequity has reduced.

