Workforce strategy	No specific pathways to support First Nations MIH workforce.	Supportive career pathways with First Nations MIH workers embedded in the team with cadetships (or similar) to support midwifery education for First Nations persons. Aboriginal Family Support Workers (or similar) work side-by-side with midwives.
Continuity	No continuity of midwifery carer through antenatal, intrapartum and postnatal continuum. Care is fragmented and women see multiple providers.	Continuity of midwifery carer networked from community to a higher-level service, offering 24/7 care from a named midwife from first presentation in pregnancy until handover to child health services 6 weeks after birth. Midwifery Group Practice (caseload) midwife providing clinical care in collaboration with the extended workforce based on need (e.g. psychologist, social worker, obstetrician, paediatricians, sexual and reproductive health).
Strengthening family capacity	No maternity programs focussed on strengthening family capacity and/or cultural connection in relation to services offered through this hospital. Women may enrol in external programs.	Programs that focus on strengthening family capacity and cultural connection in relation to MIH, integrated with the BoC service.
Place of birth	No out-of-hospital option. Hospitals do not recognise or incorporate the knowledge, values and birth aspirations of First Nations people.	During the first and second phase of the new care model, all intrapartum care will occur in hospitals. If feasible, a free-standing, community-based birth centre will be set up and available for First Nations women with uncomplicated pregnancies (Category A according to consultation and referral guidelines) [18]; women with complex pregnancies (Category B or C) will birth in the local or tertiary hospital. Birth care will incorporate traditional practice; recognise the connection with Land and Country; incorporate holistic health; value both First Nations and non-First Nations ways of knowing, learning and risk assessment; and will provide a culturally competent service.

Note: *MIH* Maternal and Infant Health

^a^Some sections reproduced from Kildea, Gao et al. [19] Permission not required under licence CC BY-NC-ND 4.0

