8	**Onset of labour** (induced, no labour, spontaneous)	MEDREC		X			
9	**Augmentation of labour** with artificial oxytocin	MEDREC		X			
10	**Place of birth** (e.g. home, birth centre, hospital)	MEDREC		X			
11	**Mode of birth** (non-instrumental vaginal birth, instrumental vaginal birth, caesarean section)	MEDREC		X			
12	**Water birth** (yes/no)	MEDREC		X			
13	**Perineal status** (intact/1st degree tear, 2nd degree tear, 3rd/4th degree tear)	MEDREC		X			
14	**Episiotomy** (yes/no)	MEDREC		X			
15	**Management of third stage labour** (active, physiological)	MEDREC		X			
16	**Postpartum hemorrhage** (blood loss < 500; 500–999; 1000–1499; 1500 ml and/or with blood transfusion	MEDREC		X DC – 6 wks			
17	**Mother admission to hospital** up to 6 weeks postpartum (yes/no)	MEDREC		X – 6 wks			
18	**Women who had a known midwife in labour and/or birth** (yes/no)	SUR			X		
19	**Birthing and maternity care experiences**	SUR QUAL	X		X	X	X
20	**Maternal parenting self-efficacy**	SUR QUAL			X	X	
*Fetal, neonatal and infant outcomes*							
21	**Low birth weight** (< 2500 g, 2500 g or more)	MEDREC		X			
22	**Birth weight** (grams, mean, sd)	MEDREC		X			
23	**Apgar score 5 minutes** (< 7, 7 or above)	MEDREC		X			
24	**Admission to a separate neonatal nursery** (yes/no)	MEDREC		X - DC			
25	**Breastfeeding status at 2 and 6 months postpartum** (exclusive, mixed, formula only, other)	SUR			X		X
26	**Infant admission to hospital up to 28 days of age** (yes/no)	MEDREC		X – 28 days			
27	**Length of facility stay for mothers and infants following birth** (mean, median, range)	MEDREC		DC			
*Social & Emotional Wellbeing outcomes/variables, Culture and Connection*							
28	The **Edinburgh Postnatal Depression Scale** (EPDS) score (could also be assessed at other timepoint(s) as clinically indicated)	MEDREC SUR	First AN visit		X		X
29	**Negative Life Events Scale** (NLES) (full extended version) score	SUR	X				X
30	The **modified Kessler psychological distress scale** (K5) score	SUR	X		X		X
31	**Women’s cultural connection and identity**	SUR QUAL	X			X	X
*Acceptability, safety and satisfaction*							
32	The **feasibility and acceptability of an established Birth Centre** assessed by the proportion of eligible women in Birthing on Country care who start labour in the birth centre	MEDREC QUAL		X		X	
33	The **proportion of women who transferred from the birth centre**/model of care at any time and for any reason	MEDREC		X DC			
*Cost outcomes*							

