34	**Mean cost of care per mother/infant pair** Health economic evaluation takes a health system perspective and will conduct a cost-effectiveness analysis. Costs to be included are antenatal care, birth, postnatal care costs; readmissions costs within 6 weeks postpartum; infants’ special care nursery and readmission.		First AN visit	Until 6 weeks (mother) 28 days (baby)			

Key: *DC* Discharge (from hospital/birth centre etc), *MEDREC* Medical/maternity/obstetric records, *QUAL* Qualitative data collected via audio recorded, one-to-one yarns (a type of narrative interviewing), unstructured/semi-structured interviews, yarning circles (a type of focus group discussion), researcher field notes, *Sd* Standard deviation, SUR Questionnaires (surveys) designed for this study, *Wk* week

Notes

1. All tools/scales will be scored according to their recommended guidelines and outcomes reported accordingly

2. All items measured for both intervention and standard care groups

3. The time period under consideration for the innovation is from the first day of pregnancy until handover to child health services at 6 weeks postpartum, however the study is longitudinal following mothers and babies until 6 months

4. Please see Additional File 2 for more detail on scales and tools used in women’s surveys

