### Study participants & eligibility

#### Inclusion/exclusion criteria

##### Cohort study

Routinely collected data will be extracted for all women within the historical and intervention time periods who gave birth (or were booked to give birth) to a First Nations baby in the study sites (2013–2022). Exclusions will be based on standard and/or previously used methods to ensure validity and rigour.

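### The grouping rule does not say when a woman's model of care is fixed; if it is fixed at birth, exits from the new service can bias the preterm comparison in its favour

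*Protocol article*

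**What the plan says.** The section on health services and other routinely collected data (protocol article, Quantitative data) holds the only explicit grouping rule for the clinical outcomes: data from all women "will be extracted and analysed by birth model of care". No time of assignment is given. The same section says the analyses will "compare maternal and infant health outcomes between the baseline cohort (both sites) and Birthing on Country service innovation cohort (both sites"), and then adds further comparisons: "as well as standard care/concurrent and historical control groups, and non-First Nations groups (where available"). Other sections also describe the groups by care received: Study components refers to women getting their care through the two services, and Power and sample sizes counts births among those attending the new service.

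Table 2, outcome 33, is the proportion of women who transferred from the birth centre or "model of care at any time and for any reason". No expected proportion is given, and the article does not say in which group these women are analysed.

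Three other places bear on the question. In Table 1, the Birthing on Country column says that "women with complex pregnancies (Category B or C) will birth in the local or tertiary hospital", and describes the service as "offering 24/7 care from a named midwife from first presentation in pregnancy until handover to child health services 6 weeks after birth". Note 3 to Table 2 says "The time period under consideration for the innovation is from the first day of pregnancy until handover" at six weeks. The cohort inclusion rule takes women who "gave birth (or were booked to give birth) to a First Nations baby in the study sites"; this settles who enters the dataset, not which group they join.

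**The concern.** If group is set by the model a woman is in when she gives birth, membership is decided after pregnancy complications may have appeared. Women who leave the service may well be at higher risk of preterm birth than those who stay. Losing them lowers the preterm rate in the innovation cohort without any effect of care. The historical controls had no such service to leave, so the selection acts on one side only. In the concurrent comparison the same women could also raise the control rate.

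Preterm birth drives the sample size. Normal birth and healthy baby both require at least 37 weeks, so a bias in preterm birth carries into them.

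The planned adjustment, including propensity matching on pregnancy complications, would not reliably remove this. Such complications can arise after entry to the service and can cause the transfer. Conditioning on them does not restore the group as booked, and may remove part of a real effect.

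**Working it through.** **The plan's own figure.** Inputs from Power and sample sizes: control rate 12.9%, a 50% reduction (to 6.45%), 80% power, 5% type 1 error (taken as two-sided), 70:30 split, 7% exclusions, 10% missing. The two-proportion formula without continuity correction gives 572 controls, so 572/0.70 = 817 in total. Inflated, 817/(0.93 × 0.90) = 976, or 817/0.83 = about 985. Both are close to the stated 983 (687 + 296), so the inputs are read correctly.

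**Bias with no true effect.** The overall risk is 0.129 in every group as booked. Let L be the share who leave the new service and R the ratio of leavers' to stayers' preterm risk. Both are assumptions, because the article gives neither.

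- Stayers' risk: s = 0.129/(1 − L + L × R). Leavers' risk: R × s.
- Against historical controls (removal only): OR = [s/(1 − s)]/[0.129/0.871].
- Against a concurrent group assumed equal in size before transfers (removal plus reclassification): control risk c = (0.129 + L × R × s)/(1 + L), and OR = [s/(1 − s)]/[c/(1 − c)].

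Worked case, L = 0.10 and R = 3: s = 0.129/1.20 = 0.1075 and leavers' risk = 0.3225. Historical OR = 0.1204/0.1481 = 0.81. Then c = (0.129 + 0.03225)/1.10 = 0.1466, and concurrent OR = 0.1204/0.1718 = 0.70.

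The chance of a false benefit uses the planned rural sizes less losses: 687 × 0.837 = 575 historical and 296 × 0.837 = 248 innovation women, the latter multiplied by (1 − L). The concurrent group is 248 × (1 + L). The nominal chance in this direction is 2.5%.

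| L | R | OR, historical | False benefit | OR, concurrent | False benefit |
|---|---|---|---|---|---|
| 5% | 2 | 0.95 | 4% | 0.90 | 6% |
| 5% | 3 | 0.90 | 6% | 0.82 | 11% |
| 10% | 2 | 0.90 | 6% | 0.83 | 10% |
| 10% | 3 | 0.81 | 12% | 0.70 | 25% |
| 20% | 3 | 0.69 | 27% | 0.56 | 52% |
| 10% | 5 | 0.69 | 29% | 0.54 | 60% |

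**What a large artefact would need.** Setting s/0.129 to a target risk ratio T gives L = (1/T − 1)/(R − 1). To mimic the planned halving against historical controls, L must be 50% at R = 3 or 25% at R = 5.

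**With group fixed at first booking.** Under the same model L has no effect on membership: OR is 1.00 against both comparators, the chance of a false benefit is 2.5%, and the required sample size is unchanged.

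**The case against.** The strongest reply is that the phrase is ambiguous and much of the article points away from a grouping fixed at delivery. Table 1 places complex pregnancies in hospital for birth within the new service, with the named midwife continuing to six weeks. The innovation is dated from the first day of pregnancy. Inclusion covers women who were only booked. Outcome 33 mixes birth-centre transfers with exits from the model, and reporting it requires transferred women to remain identifiable. The detailed rule may also stand in a full protocol or SAP that is not shown.

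Much of this stands. A reader might infer that the plan counts women who leave as standard care; no section says so. A reader might also take any hospital birth or complex pregnancy as an exit; Table 1 says otherwise. Nor can women who leave move into a cohort from earlier years, so reclassification can touch only the concurrent comparison. Against historical controls only removal operates, and it is the smaller bias.

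A third tempting inference is that this mechanism alone could reproduce the 37% preterm reduction reported for the predecessor service. It can be made to: with 15% leaving at 40% risk, the stayers' risk is (0.129 − 0.060)/0.85 = 8.1%, a risk ratio of 0.63. But that puts 0.060/0.129 = 47% of all preterm births among the leavers, at about 4.9 times the stayers' risk. Nothing in the article supports such figures.

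What does not stand is that this is mere silence left to a fuller document. The article states a grouping rule, expects women to leave the model, and words the rule so that its natural reading fixes the group too late.

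**Conclusion.** The concern holds as a defect in the stated rule, not as proof that the analysis will be biased. Under the natural reading and modest assumed transfers (5% to 10% at three times the stayers' risk), the distortion of the odds ratio is roughly 10% to 19% against historical controls. It is roughly 18% to 30% against an equal-sized concurrent group if leavers are counted there. Larger distortions need more extreme assumptions. The sizes rest on the 12.9% rural rate, on transfer shares and risks that the article does not supply, and, for the concurrent figures, on equal group sizes before transfers. If few women leave, or their risk is close to the stayers', the bias is small. The concurrent comparison still matters, because the primary hypothesis names a standard care cohort where one is available. This should be fixed before analysis, but it does not undermine the design.

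**What to change.** Replace the grouping phrase with a dated rule: each woman is analysed in the model of care recorded at her first booking and stays in that group for all primary outcomes, whatever transfer or place of birth follows. Report model at birth, and the transfers counted under outcome 33, as secondary description only.

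The cost is one variable derived from booking information. The sections on Waiver and Participant database already provide for merging the data sources under a unique study number. Sample size does not change. The price is that the estimate includes women who left the service and so may be smaller than one restricted to those who stayed. The rule does not deal with differences between women who choose one service or the other at booking; the planned adjustment is still needed for those, using characteristics known at that time.
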